#### Extension Study: Months 6, 9, and 12 Visits (±1 Week)—If Participating in Optional Extension Study

Participants entering the optional extension may attend follow-up visits at month 6 (week 24 ±1 wk), month 9 (week 36 ±1 wk), and month 12 (week 52 ±1 wk). At the month 6 and month 9 visits, participants will verbally confirm their willingness to continue. Changes in concurrent medications and any AEs since the previous visit will be recorded at each visit. A researcher will assess the 28-joint tender and swollen joint counts and the patient and physician visual analog scales. CRP results obtained through routine clinical care will also be recorded to calculate the DAS28-CRP. Participants will complete the HAQ-DI and a paper RA-FQ unless they have completed the online RA-FQ within the preceding 24 hours.

A clinically confirmed flare will be defined as a DAS28-CRP of ≥2.4 and/or at least 1 swollen joint attributable to inflammatory RA activity. Confirmed flares will be managed by the ROADMAP clinical team as part of routine care, and the study investigator will record the estimated date of flare onset. At each visit, completed paper questionnaires and Axivity AX6 devices from the preceding monitoring period will be collected. Participants who do not wish to continue at month 6 or month 9 will complete the wearable usability and acceptability questionnaire and exit the study. All participants remaining in the study at month 12 will complete the questionnaire and exit the study. No participant will be followed for more than 12 months from baseline. These optional extension visits will be implemented only after approval of the submitted ethics amendment and all required sponsor and site approvals.

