#### Ad Hoc Flare Visits (Throughout the Study)

Patients tapering their DMARDs in the ROADMAP clinic may request additional ad hoc visits outside the usual 3-monthly schedules if they suspect an arthritis flare. There is no limit to the number of ad hoc visits, although in practice only one ad hoc visit would usually be expected for a patient who experiences a flare. In these cases, the patient will contact the study team to report possible flare symptoms, and a study investigator will then contact the ROADMAP clinic administrative team to arrange a ROADMAP clinic appointment and book a study visit to coincide with it. At the start of the ad hoc visit, patients will be asked to verbally confirm their willingness to continue in the study. Any changes in concurrent medications and any AEs since the last clinic visit will be recorded. A researcher will then assess the 28 joint tender and swollen counts, patient visual analog scale, and physician visual analog scale required for DAS28-CRP disease activity assessment. CRP blood test results obtained during routine clinical care at the ROADMAP clinic visit will also be recorded for DAS28-CRP calculation. The patient will then complete an HAQ-DI questionnaire and an RA-FQ paper questionnaire, unless an online RA-FQ has already been completed within the previous 24 hours.

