### Delay to Final DAS28-CRP Calculation

As the DAS28-CRP calculation includes the CRP blood test result, the final DAS28-CRP score can only be fully calculated when the CRP result is available (ie, after conclusion of each study visit). Partial DAS28-CRP scores can be calculated at the time of the study visit and are usually indicative of final flare or remission status. However, it is possible that unexpected elevation of the CRP result may push the final DAS28-CRP score above the remission threshold and thus change the flare or remission status after the study visit has been completed. If this occurs at the baseline visit, then the patient would become ineligible to continue and should be withdrawn from the study at this point. If this occurs at a follow-up visit, the patient will continue with the Axivity AX6 and RA-FQ monitoring and follow-up schedule that was arranged in their recently completed study visit. Any necessary changes to clinical management will be arranged by the ROADMAP clinical team as per usual clinical care.

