### Primary Analyses

The primary outcome is the time from study enrollment to the first clinically confirmed RA flare, defined as a DAS28-CRP of 2.4 or above.

The primary objective of the study is to predict clinically confirmed flare risk using dynamic risk prediction methods based on daily accelerometry data including both the quality metrics and the physical activity measures. In addition, we would like to retrospectively assess the accuracy of the model vs patient-reported flare.

We will use landmarking models to develop a dynamic risk prediction approach for arthritis flare. Landmarking is a time-updated survival modeling framework that generates risk predictions at predefined time points (landmark times) using information available up to each time point. Predictions are then made over specified future time horizons.

The approach consists of two components:

A longitudinal submodel, which summarizes repeated accelerometry-derived measurements over timeA time-to-event submodel, which estimates the risk of flare from each landmark time

At each landmark time, the longitudinal submodel is used to extract summary measures of the accelerometry data up to that time, and these summaries are then included as predictors in the time-to-event model to estimate the future risk of flare.

The event of interest is the first clinically confirmed arthritis flare. Participants who do not experience a clinically confirmed flare will be censored at the end of their individual follow-up period or at earlier withdrawal.

For the time-to-event component, we will fit both Cox proportional hazards models and random survival forests (RSFs) to assess potential improvements in predictive performance and capture potential nonlinear relationships and interactions. We also consider including variables such as age, sex, Clinical Frailty Score, and anticitrullinated protein antibodies (ACPAs) antibody status (either positive/negative or the actual titer) as fixed effects or variables in both longitudinal and time-to-event submodels as they are clinically important.

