The model will be generated at weekly landmark times throughout follow-up. At each landmark, the model will use all accelerometry data collected up to that time to estimate the probability of clinician-defined flare occurring within the subsequent 14 days. Weekly updating allows risk estimates to be refreshed throughout DMARD tapering and provides clinically actionable information to support decisions regarding continuation or modification of tapering.

We will also evaluate the accuracy of the model’s flare predictions for each prediction time window against patient-reported flares derived from the RA-FQ, based on responses to the yes or no question about current flare status. Patient-reported flare status will serve as the reference standard. Model-predicted flares will be compared against patient reports to calculate sensitivity, specificity, and agreement (Cohen κ). It helps to assess how well the model’s predictions align with patient perception.

Sensitivity: proportion of patient-reported flares that are correctly predicted by the model (true-positive rate); higher values, close to 100%, are desirable.Specificity: proportion of patient-reported nonflares that are correctly identified as no flare by the model (true-negative rate); higher values, close to 100%, are desirable.Agreement: measured using Cohen κ to quantify concordance between model-predicted and patient-reported flares; higher values, close to 1, indicate stronger agreement beyond chance.

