### Strength and Limitations

The main strength of this study is its embedding within an existing NHS DMARD tapering service, which improves real-world relevance and feasibility. Study visits are aligned with routine ROADMAP clinic appointments to reduce patient burden, and ad hoc flare visits are incorporated to capture clinically meaningful events when they occur. The protocol also includes practical accommodations for patients who cannot use the REDCap portal by offering paper RA-FQs, which may improve inclusivity and reduce avoidable exclusion related to digital access. Another strength is the multimodal design, combining clinician assessment, PROMs, and continuous wearable data. This supports richer phenotyping of flare-related change and may improve prediction performance compared with relying on any single data stream alone. The planned diagnostic evaluation using AUC, sensitivity, specificity, and predictive values is also appropriate for assessing clinical utility in an early development phase.

The protocol also has limitations. It is a single-site observational study, so external validity may be limited, and the findings may reflect local service pathways, patient selection, and tapering practices. The target sample is intended to support model development and pilot evidence rather than definitive effectiveness conclusions. In addition, flare classification depends partly on clinical review timing, which may introduce timing uncertainty in the reference outcome. The protocol acknowledges this and includes procedures for delayed final classification and investigator clinical discretion when the DAS28-CRP is elevated for reasons unrelated to inflammatory arthritis.

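### The primary model predicts flare within 14 days, but flares are confirmed only at visits 12 to 16 weeks apart or on request, and the article does not say which date is the event date

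*Protocol article*

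**What the plan says.** Under Primary Analyses, "The primary outcome is the time from study enrollment to the first clinically confirmed RA flare". Cox models and random survival forests are fitted, and participants without a confirmed flare are censored at the end of follow-up or at withdrawal. Interval censoring is not mentioned. "The model will be generated at weekly landmark times throughout follow-up". On the inputs to each weekly prediction, the section says that "the model will use all accelerometry data collected up to that time". The target of each prediction is short-term risk: the purpose is to "estimate the probability of clinician-defined flare occurring within the subsequent 14 days". Predictor data are not cut at flare onset. The Methods paragraph of the Abstract measures lead time back from the clinically confirmed flare.

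Scheduled examinations fall at week 12 (Month 3 Visit) and, in the optional extension, at weeks 24, 36 and 52. Otherwise patients "may request additional ad hoc visits outside the usual 3-monthly schedules if they suspect an arthritis flare". When a flare is confirmed at an extension visit, "the study investigator will record the estimated date of flare onset"; the Month 3 and Ad Hoc Flare Visits sections say the same. No analysis section refers to that date.

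Strength and Limitations concedes that "flare classification depends partly on clinical review timing, which may introduce timing uncertainty in the reference outcome", and names delayed final classification and investigator discretion as the procedures that deal with it.

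**The concern.** A 14-day horizon is set against a reference standard that, without a patient request, is observed every 12 to 16 weeks. If the event is dated at the confirming visit, two things follow.

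- A landmark that falls during a flare, but more than 14 days before anyone examines the patient, is labelled non-flare. A correct alarm at that landmark is scored as a false positive.
- Many landmarks labelled positive fall after the flare has begun, so the model is credited with predicting something already under way.

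Events would also cluster at scheduled visits, so nearness to a visit could itself drive predicted risk. The AUC, which Target Recruitment Sample Size tests against 0.6, and the lead time would then partly measure the visit calendar and patients' help-seeking. The labels would be poorest for patients who do not ask for a visit, for whom remote monitoring matters most.

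The two procedures named as safeguards decide whether a flare counts. Neither addresses when it began.

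**Working it through.** The article gives no figure for this point, so there is nothing to reproduce. The check works out what confirmation dating would do.

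**Inputs from the article.** Horizon 14 days; landmarks every 7 days; examinations at baseline and weeks 12, 24, 36 and 52, hence gaps of 12, 12, 12 and 16 weeks (84, 84, 84 and 112 days); ad hoc visits on request.

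**Assumptions (not in the article).** Onset is uniform within a gap. A share p of patients asks for a visit after an exponential delay with mean 7 or 14 days, and is seen at the next scheduled visit if that comes first. The rest are confirmed at the next scheduled visit.

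**Scheduled visits only, 84-day gap.** Landmarks lie at days 7k, k = 0 to 11, and the visit is on day 84.

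1. Mean lag from onset to confirmation: 84/2 = 42 days. Share of flares with a lag over 14 days: 70/84 = 83%.
2. Only the landmarks at days 70 and 77 have the visit within 14 days, so 2 of 12 are positive.
3. The landmark at day 7k falls after onset with probability 7k/84 = k/12. Positive landmarks after onset: (10/12 + 11/12)/2 = 1.75/2 = 87.5%.
4. Ongoing-flare landmarks per flare: (0 + 1 + … + 11)/12 = 66/12 = 5.5.
5. Of these, labelled non-flare (k = 0 to 9): 45/12 = 3.75 per flare, and 3.75/5.5 = 68%.

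**Scheduled visits only, 112-day gap (weeks 36 to 52).** With k = 0 to 15 and probability k/16: mean lag 112/2 = 56 days; positive landmarks after onset (14/16 + 15/16)/2 = 91%; ongoing-flare landmarks 120/16 = 7.5, of which 91/16 = 5.69 are labelled non-flare, or 76%.

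**With ad hoc visits, 84-day gap** (simulation, 200,000 flares per scenario; each cell gives mean delay 7 days / 14 days):

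| Share asking | Mean lag, days | Positive landmarks after onset | Ongoing-flare landmarks labelled non-flare | Such landmarks per flare |
|---|---|---|---|---|
| 50% | 24.3 / 26.9 | 64% / 72% | 60% / 59% | 1.93 / 2.10 |
| 90% | 10.0 / 14.7 | 44% / 60% | 35% / 40% | 0.46 / 0.78 |
| 100% | 6.4 / 11.7 | 39% / 56% | 11% / 29% | 0.10 / 0.46 |

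The mean lags can be checked by hand. For patients who ask with mean delay d, the capped mean is d[1 − (d/84)(1 − e^(−84/d))], which gives 6.4 for d = 7 and 11.7 for d = 14. At 90% asking, 0.9 × 6.4 + 0.1 × 42 = 10.0 and 0.9 × 11.7 + 0.1 × 42 = 14.7.

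Both effects are present in every scenario, but their size depends strongly on how many patients ask and how quickly.

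**If events were dated at true onset,** no landmark after onset would remain in the risk set, and both effects would be zero by construction. With the recorded onset date, the error of a retrospective estimate remains; the article gives no figure for it.

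**The case against.** The strongest reply is that the article never says that flares are dated at confirmation. A reader might infer it as a rule, but the phrase about clinical confirmation can be read as defining which flares count, an onset date is collected, and the choice may sit in an analysis plan that is not shown. This stands as a limit on the claim. What remains is that the outcome wording and the lead-time anchor point to confirmation, and nothing in the article points to onset.

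Second, a reader might infer that any use of post-onset data is an error. The article does not support that. Its Objective speaks of detecting flare, and Principal Findings speaks of risk before or around a confirmed flare. Recognising a flare before the clinic confirms it is a legitimate aim, so discarding every landmark between onset and confirmation would lose relevant evidence. Even so, those landmarks cannot serve as flare-free controls under either aim.

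Third, the scheduled-visit figures, including the 83% of flares with a lag over 14 days, are a worst case for an 84-day gap. The Ad Hoc Flare Visits section expects that a patient who flares will usually have one such visit. This stands, and the headline size should not rest on those figures alone.

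Fourth, a reader might infer that flares recognised through a late CRP result get no onset date. The section on delayed calculation says only that "If this occurs at a follow-up visit, the patient will continue with the Axivity AX6 and RA-FQ monitoring" as already scheduled. It is silent on the onset date and does not rule it out.

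Finally, the weekly RA-FQ flare item is a denser reference and is used in separate comparisons. It reports the patient's view and does not date the clinical flare.

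**Conclusion.** The concern holds in a limited form. The article combines a 14-day horizon and weekly landmarks with an outcome seen only at 12- to 16-week visits or on request. It fits models that treat the event time as exact, does not name the event date, and gives the recorded onset date no analytic role.

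If confirmation is the event date, as the wording suggests, ongoing flares become controls, and early detection is mixed with prediction. With uniform onset in an 84-day gap, the share of ongoing-flare landmarks labelled non-flare runs from 68% (scheduled visits only) to 35–40% (90% asking) and 11–29% (all asking). The share of positive landmarks after onset runs from 87.5% to 44–60% and 39–56%. The 16-week gap is worse, though it arises only if the extension to 12 months is approved. Ad hoc uptake, its delay and uniform onset are assumptions. The article admits timing uncertainty, but the procedures it names do not reduce it. The plan should be changed before analysis.

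**What to change.** - Name the event date in the primary analysis.
- Do not count landmarks between estimated onset and confirmation as flare-free controls.
- Report performance separately for landmarks before onset (prediction) and from onset to confirmation (early detection).
- Report lead time relative to both onset and confirmation.
- Make sure that the onset date is also recorded for flares confirmed by a late CRP result.
- Fit the model three ways: with recorded onset, with onset interval-censored between the last flare-free examination and confirmation, and with the confirmation date. Declare one primary and the others sensitivity analyses.

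Which version is primary is open to debate. Recorded onset is retrospective and carries recall error, probably largest in flares that the patient did not notice. The interval-censored analysis avoids that date; it does not bound its error.

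The cost is analysis-plan wording, a check that one existing field is completed in late-CRP cases, and slightly more analysis work. With 16 of 100 patients recruited by July 1, 2026, the change is cheap now. Onset dates not recorded at the time are hard to recover later.

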##### RA-FQ

The RA-FQ is also designed to remotely monitor patients with RA during drug tapering. Participants rate, on a 0‐10 scale, their pain, difficulty with physical activities, fatigue, joint stiffness, and challenges in daily activities such as work, over the past week. At the end of the questionnaire, 2 yes or no questions ask whether the patient has experienced these symptoms for more than 1 week and whether they believe they are currently experiencing a flare of RA. The responses provide a standardized way to assess symptom severity and detect flares, helping clinicians track disease activity and adjust treatment if needed. The questionnaire will be collected weekly for each patient. For the 0‐10 scale items, the average score for each symptom will be calculated across all patients at 4 main visit time points, and summary statistics (eg, mean, SD, and/or median, IQR, and range) will be reported.

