### Missing Data

If any accelerometry-driven data are missing for a patient, the last observation carried forward (LOCF) method will be applied, as these data are collected daily and LOCF reflects the information available at the time of prediction. For the RA-FQ, if any item is missing for a patient, it will be replaced using the LOCF method, as the questionnaire is collected weekly.

For quantitative feedback from the participant acceptability questionnaire, missing responses in Section A will not be imputed, as they reflect participants’ perceptions at the time of data collection. For the overall satisfaction score (0‐100), missing values will also not be imputed, and analyses will be based on observed data only.

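### Predictions of a new flare within 14 days are scored against current self-reported flare status, so the accuracy figures mix detecting an existing flare with predicting a new one

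*Protocol article*

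**What the plan says.** All references are to the protocol article.

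- **What is predicted.** Under Primary Analyses: "The event of interest is the first clinically confirmed arthritis flare". On timing: "The model will be generated at weekly landmark times throughout follow-up". At each landmark the model is to "estimate the probability of clinician-defined flare occurring within the subsequent 14 days".
- **What it is scored against.** The same section compares the model's "flare predictions for each prediction time window against patient-reported flares derived from the RA-FQ", and these are "based on responses to the yes or no question about current flare status". It adds: "Patient-reported flare status will serve as the reference standard". The statistics are sensitivity, specificity and Cohen κ.
- **What the item asks.** The RA-FQ section describes a weekly questionnaire. One of its two closing yes/no questions asks patients "whether they believe they are currently experiencing a flare of RA".
- **Missing answers.** Under Missing Data: "For the RA-FQ, if any item is missing for a patient, it will be replaced using the LOCF method".
- **Status.** Textbox 1 lists the comparison with patient-reported flare as a primary subobjective.

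None of these sections limits the reference to newly reported flares, or removes windows in which the patient already reports flare at the landmark.

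**The concern.** The model answers whether a first confirmed flare will start in the next two weeks. The reference answers whether the patient feels in flare at the time of asking. A flare that the patient has already reported cannot be predicted, only detected. When both kinds of window enter one two-by-two table, the sensitivity and κ describe neither task, and longer episodes carry more weight because they fill more windows.

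The result would be read as predictive accuracy against patient-reported flare, which is a primary subobjective. Secondary Analyses then compares these models with models refitted to patient-reported flare, to judge whether the accelerometry signal holds across flare definitions. The same mixture would enter that conclusion.

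**Working it through.** The plan gives no figure for this comparison, so there is none to reproduce. Its one design calculation (100 patients, AUC 0.8 against 0.6) concerns a different quantity.

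**1. Target and reference side by side**

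| | Model | Reference |
|---|---|---|
| Event | first clinically confirmed flare | patient's yes/no answer on flare now |
| Type | incident, after the landmark | prevalent state |
| Timing | 14-day window, weekly landmarks | weekly questionnaire |
| Already in flare at landmark | out of the risk set, if clinically confirmed | no exclusion stated |

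**2. Can a self-reported flare persist in the risk set?** Yes. Apart from withdrawal and end of follow-up, only a clinically confirmed flare ends time at risk. Routine visits are about 3 months apart, and ad hoc visits depend on the patient asking. If flare is not confirmed at an ad hoc visit, monitoring continues on the current schedule. Under Clinical Discretion, a raised DAS28-CRP may also be discounted.

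**3. Counting windows.** Assume that a window is positive if either of the two weekly answers after the landmark is 'yes', and that the participant stays at risk throughout. Let the 'yes' answers fall in weeks w to w+d−1.

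- Positive landmarks run from w−2 to w+d−2, which is d+1 landmarks.
- Two of them (w−2 and w−1) precede the first 'yes'.
- The other d−1 begin once the first 'yes' has been given, a share of (d−1)/(d+1).

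For d = 1 this is 0/2 = 0%, for d = 2 it is 1/3 = 33%, and for d = 4 it is 3/5 = 60%. The documents give no episode length, so d is assumed.

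**4. Effect on sensitivity.** Pooled sensitivity = Se_new × 2/(d+1) + Se_ongoing × (d−1)/(d+1). Take Se_new = 0.50 (assumed) and vary Se_ongoing (assumed):

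| d | Se_ongoing 0.80 | 0.50 | 0.30 |
|---|---|---|---|
| 1 | 0.50 | 0.50 | 0.50 |
| 2 | 0.333 + 0.267 = 0.60 | 0.50 | 0.333 + 0.100 = 0.43 |
| 4 | 0.20 + 0.48 = 0.68 | 0.50 | 0.20 + 0.18 = 0.38 |

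The sign depends only on whether ongoing flares are flagged more or less often than new ones.

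**5. Sensitivity to the window convention.** A simulation that also counted a 'yes' given at the landmark itself used these assumptions: weekly onset hazard 0.0133, false-alarm rate 15%, new flares flagged 50% of the time, and self-reported flare lasting 1 to 12 weeks before the patient leaves the risk set. Ongoing flares then made up about 33% (1 week), 50% (2 weeks), 66% (4 weeks) and 84% (12 weeks) of positive windows. Scored on new onsets only, sensitivity was about 0.50 and κ about 0.10. With ongoing flares included:

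| Ongoing flares flagged | Sensitivity, 1 to 12 weeks | κ, 1 to 12 weeks |
|---|---|---|
| 80% | 0.59 to 0.76 | 0.17 to 0.48 |
| 50% | 0.50 | 0.14 to 0.30 |
| 30% | 0.43 to 0.33 | 0.11 to 0.17 |

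κ moved even where sensitivity did not, because the share of positive windows changed. Specificity stayed at 0.85: the negative windows are the same under both scorings here, and the false-alarm rate was fixed. Under the step 3 convention, specificity is touched only at the landmark of the last 'yes'. That window is negative although the patient reported flare at its start.

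**6. Carry-forward.** The yes/no flare question belongs to the RA-FQ, and the rule covers any item. Taken literally, an unanswered week would inherit the previous answer. That could lengthen an episode or hide its onset in the reference itself.

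**The case against.** **Purpose.** The section says the comparison shows how closely predictions match what patients perceive, and κ is an agreement statistic. Agreement with a current state is a legitimate question, and dropping participants already in flare would hide lasting disagreement between patient and clinician. This stands as a reason to keep a concurrent analysis. It does not justify presenting the mixture as predictive accuracy.

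**Detail left to the SAP.** How weekly answers map to windows, and how repeats count, may be set out in an analysis plan that is not shown. The article defines sensitivity in terms of flares, which could mean episodes. That leaves the unit open and makes the counts above conditional. But the article itself fixes the reference item, its role, comparison by window and the carry-forward rule, and on those terms ongoing flares are included.

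**Ad hoc visits.** Patients who suspect flare can ask for review without limit, and a confirmed flare ends their time at risk. This shortens d, and d = 1 gives no ongoing share under the step 3 convention. It does not cover patients who do not ask, or whose flare is not confirmed.

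**Carry-forward.** The RA-FQ section treats the 0–10 items separately from the yes/no questions, so the rule may be meant only for the former. The wording does not say so, and the point is put only as a possibility.

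**A stronger reading.** A reader might infer that ongoing self-reported flares automatically count as correct predictions and so inflate sensitivity. The documents do not support that. Such a window is a true positive only if the model flags it; otherwise it is a false negative.

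**Conclusion.** The point holds as a mismatch between an incident target and a prevalent reference in a primary subobjective, with no exclusion of flares already reported at the landmark. Its size depends on assumptions that the article does not settle: the length of self-reported episodes, how often ongoing flares are flagged, and which answers belong to a window. If any later 'yes' in the window counts, the share of positive windows that are not predictions is 0% for a single 'yes', 33% for two and 60% for four. The bias in sensitivity has no fixed direction. κ is also affected, and specificity least.

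The reach is limited to this comparison and the robustness argument that draws on it. A reader might infer that the prediction model or the AUC hypothesis behind the sample size is compromised. Neither is, because both rest on clinically confirmed flare.

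**What to change.** For predictive accuracy against patient-reported flare:

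- At each landmark, include only participants whose latest observed RA-FQ flare answer is 'no' and who have had no clinically confirmed flare.
- Define reference-positive as a first 'yes' within the following 14 days.
- Exempt the yes/no flare item from carry-forward when it serves as the reference standard.
- Allow for overlapping windows from the same participant, for example by resampling participants when forming intervals.

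Report agreement with ongoing self-reported flare as a separate analysis, labelled as concurrent agreement.

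This needs analysis wording and a risk-set filter, with no new data. The price is precision. Under the step 3 convention, an episode of four 'yes' answers would contribute two positive windows instead of five, so intervals will be wider.
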